### Criteria for discontinuing or modifying allocated interventions {11b}

N/A; no criteria for interruption or modification of allocated interventions.

### Strategies to improve adherence to interventions {11c}

N/A; no strategies to improve adherence to interventions.

### Relevant concomitant care permitted or prohibited during the trial {11d}

Other rehabilitation modalities necessary for the patient are allowed (occupational therapy, speech therapy, neuropsychology) and drug treatments are allowed.

No procedure is forbidden, except for the introduction of additional physiotherapy sessions that could lead to an imbalance in the amount of rehabilitation between the 2 groups.

### Provisions for post-trial care {30}

N/A; no provisions for post-trial care.

### Outcomes {12}

All testing sessions will be conducted by one physical therapist and one research assistant (per centre). Both evaluators will be blinded to the treatment.

Clinical and physical outcome measurements will be administered to the patients at baseline, immediately after 6 weeks of treatment, 6 months and 1 year after treatment (Fig. 1).

**Fig. 1 Fig1:**
[figure not shown]
Schedule of enrolment, intervention, assessment and follow-up

The *primary outcome* is defined as walking speed measured over 10 m at the end of the intervention (6 weeks).

The *secondary outcome* includes social participation evaluated at 6 months and 1 year, walking spatiotemporal parameters measured at each visit, walking speed measured at 6 months and 1 year, along with dorsiflexor strength evaluated at each visit.

The use of technical aids to walk and the number of falls will be described.

Finally, correlations between walking speed/dorsiflexor muscle strength and walking speed/social participation will be studied.

#### Outcome measurements

*Walking speed* will be evaluated by a 10-m walking test (10MWT). The 10MWT is a functional evaluation tool that can be easily used in clinical practice. The participants will walk this distance at a comfortable speed. Considering the initial acceleration and the last deceleration, the patients start walking 2 m before and stop 2 m after the start of the measurement. The walking time for a 10-m distance will be repeatedly measured three times, and the mean value will be selected for analysis. The verbal instruction for walking at a comfortable pace is, “If I say start, walk at a comfortable pace until I say to stop”. The test-retest reliability of this method is well-documented in post-stroke patients with a good intra-class correlation coefficient (ICC) of 0.83 for Chen et al. [17] and 0.86 for Fulk et Echternach [18].

*Walking spatiotemporal parameters* will be recorded on a GAITRite mat (GAITRite Platinum; CIR Systems, USA). The electronic treadmill (7.01 m long by 0.61 m wide) used during this study consists of sensors arranged in the form of a grid (48 × 24 sensors) for a resolution of 1.27 cm × 1.27 cm. The acquisition frequency is set at 80 Hz. We will employ 4 parameters: durations of stance and swing phases, cadence and step variability. In addition to its ease of use and reliability, this system has many advantages, such as the possibility of walking with technical aids (walkers, canes). Three passages will be carried out and the average of the 3 passages will be kept and then studied. The experimenter explains each task before it is carried out and gives an example to ensure that the patient understands it correctly. The test-retest reliability of this system for measurement of spatiotemporal gait parameters was very good (ranging from 0.98 to 0.99) in post-stroke patients [19].

*Ankle muscle strength:* Dorsiflexor muscle strength will be measured with an isokinetic dynamometer (CON-TREX, Physiomed). The patient is installed on the seat of the isokinetic dynamometer. The trunk-thigh (hip) angle is set at 85°, the thigh-leg (knee) angle at 50° and the foot-leg (ankle) angle at 90°. In order to stabilise the position, the trunk, the thigh of the tested leg and the foot are strapped. The joint range for plantar flexion/dorsiflexion movement is determined for each subject, subjectively, based on how each individual feels. The dynamometer performs automatic gravity correction. The test will be carried out in concentric/concentric mode at a speed of 30°/s. Before the test, the patient will perform submaximal repetitions to warm up and for habituation. The test will consist of 3 maximum flexion/extension petitions. The data collected will be the maximum dorsiflexor peak torque. According to the systematic review by Rabelo et al. [20], the isokinetic dynamometer seems to display good reliability for use in post-stroke patients with an ICC greater than 0.8, although fewer studies have been conducted on the ankle.

*Social participation* will be evaluated with the Subjective Index of Physical and Social Outcome (SIPSO) at 6 months and at 1 year. SIPSO is a 10-question social participation questionnaire specially developed for stroke [21, 22] with a scale of 0 to 5 divided into two subscales: 5 questions relating to physical function (physical component) and 5 questions concerning the social and emotional domains (social component). The test-retest reliability of SIPSO is excellent (ICC = 0.96) and shows high validity in stroke populations [21]. Higher scores on SIPSO reflect higher levels of ambulation, mobility, leisure, social interaction and communication, along with a high level of reintegration.

### Participant timeline {13}

#### Inclusion

The inclusion visit will be conducted by the physician within 1 week of the pre-inclusion visit. It is carried out during hospitalisation, between 15 days and 3 months post-stroke. The investigator will perform a clinical examination to verify the inclusion and non-inclusion criteria. Once the criteria have been verified, the patient and investigator will sign the informed consent form.

The investigator will collect data on the patient's stroke pathology.

The clinical examination will then be completed to provide clinical scores: severity of the stroke (National Institute of Health Stroke Score; NIHSS), passive and active range of motion of the ankle (P-ROM, A-ROM: manual measurement), motor control of the injured lower limb (De Meurisse Motor Index; MI), assessment of spasticity of the posterior leg compartment (Modified Ashworth Scale; MAS), level of functional independence (Barthel index; BI) and walking autonomy (Functional Ambulation Classification; FAC) with collection of the technical aids used and the number of falls.

This clinical evaluation will be completed by instrumental evaluations: walking speed, spatiotemporal parameters and dorsiflexor muscle strength.

#### Randomisation

Eligible patients who agree to participate will be asked to give their written informed consent, and will then be randomised into the EG or CG. We will randomise the patients at the first clinical examination. The randomisation process will be ensured using a secure internet connection with access by individual user ID and password and encrypted data transmission to the randomisation platform of the Clinical Research Unit of the Limoges University Hospital. Only the study methodologist will complete and keep the randomisation list on a secure server. In the event of a computer problem, a paper randomisation list will be available. This randomisation list will not include a stratification factor. All actions carried out on this platform, along with the identity of the person who made the changes, will be automatically archived by audit trail procedure. As soon as a patient is randomised, an email will automatically be sent to all study organisers, i.e. the clinical research assistant, data manager and principal investigator. No strategy is provided for preventing a potential imbalance between intervention and control group allocation.

#### Follow-up

Regardless of the group, patients will benefit from a 1-year follow-up including 4 visits: the first and second visits will take place during patient hospitalisation. The third (at 6 months) and the fourth (at 1 year) visits will be performed as part of the patient’s usual follow-up in the physical medicine and rehabilitation centres.

At each of these visits, a doctor will perform a clinical examination, a physical therapist and a research assistant will perform the tests to obtain the necessary outcomes for the study.

### Sample size {14}

We calculated the number of subjects in reference to the study by Gharib et Rabab, 2017 [23]. The average speed is 0.58+/−0.09 m/s in the control group and 0.67+/−0.11 m/s in the experimental group. The estimated difference between the 2 groups is 0.09 m/s. For a first species risk of 0.05 and a power of 90%, bilaterally, the number of subjects required is 54 subjects (27 per group) plus 10% (to compensate for those lost to follow-up or excluded from study). The number of patients to be included is therefore 60 (30 subjects per group).

### Recruitment {15}

Five centres that are used to working together will be involved in this study. A preliminary assessment of the feasibility of the project has been carried out and has shown that these centres have all the necessary equipment and expertise for this research.

### Assignment of interventions: allocation

#### Sequence generation {16a}

Eligible patients will be randomly assigned at a 1:1 ratio to the experimental or control group using a web-based randomisation system.

#### Concealment mechanism {16b}

Randomisation will be centralised using the randomisation platform of the Centre d’Epidémiologie, de Biostatistique et de Méthodologie de la Recherche of the Limoges University Hospital (CEBIMER) and will be conducted over a secure internet connection. In the event of a computer problem, a paper randomisation list will be available.

#### Implementation {16c}

When an investigator wishes to perform the randomisation after verifying the eligibility of a participant, he/she logs onto the platform website. The investigator completes the “randomisation” web page after having previously confirmed all of the eligibility criteria of the participant on the site. After validation of the content, randomisation is carried out and the site immediately communicates to the investigator the result of the randomisation, in particular the procedure group allocated to the participant.

### Assignment of interventions: Blinding

#### Who will be blinded {17a}

The design is open label: investigators and patients will be aware of group allocation with only outcome assessors being blinded. Evaluators will be blinded. They will not know whether the patient is included in EG or CG. Data analysts will be blinded.

#### Procedure for unblinding if needed {17b}

N/A: the design is open label with only outcome assessors being blinded so unblinding will not occur.

### Data collection and management

#### Plans for assessment and collection of outcomes {18a}

The investigators will collect data in the Ennov Clinical eCRF. Ennov clinical is a software application for clinical trial data management which uses the ORACLE database.

Patient data will be entered into the database by each user via an online portal. Each user will log onto the secure URL with a user name and a password which grants them specific viewing and editing rights (depending on the user’s profile).

The database will be hosted on the platform of the Centre d’Epidémiologie, de Biostatistique et de Méthodologie de la Recherche of the Limoges University Hospital (CEBIMER) in the Limoges Hospital. Data will be saved in real time and archived every day as computer files and on a protected hard-drive.

#### Plans to promote participant retention and complete follow-up {18b}

Patient follow-up data is entered into the eCRF and the end of research is documented, including reasons for premature discharge.

#### Data management {19}

Data will be managed by the CEBIMER. The data will be entered online by the investigators after logging onto the study database, which will be created by a data manager using the Ennov Clinical software. The quality of data entry will be ensured by consistency tests configured and generated by the data manager. If an element is incorrectly completed, validation messages will be sent to the investigator.

The WAKE trial will have on-site monitoring. An initial monitoring visit is planned for all participating centres at the start of the inclusion period. All centres will be visited by independent monitors according to the pace of recruitment. The monitor will check the informed consent forms, the consistency of the data entered with the source data and whether the inclusion and non-inclusion criteria were followed.

#### Confidentiality {27}

Authorised University Hospital staff and health authorities may have direct access to patients’ medical records in order to check the accuracy of the data collected. All these individuals are subject to professional secrecy. Medical records identifying the patient will be kept in the hospital and remain confidential.

#### Plans for collection, laboratory evaluation and storage of biological specimens for genetic or molecular analysis in this trial/future use {33}

N/A; no collection, laboratory evaluation or storage of biological specimens for genetic or molecular analysis.

## Statistical methods

### Statistical methods for primary and secondary outcomes {20a}

The statistical analysis will be performed by the CEBIMER (Centre d’Epidémiologie, de Biostatistique et de Méthodologie de la Recherche) of the Limoges University Hospital using SAS software V9.3 (SAS Institute, Cary, NC).

#### Primary endpoint analysis

The comparison of the mean walking speed over 10 m measured at the end of the intervention (week 6) will be done by a Student’s *t* test if the variable follows a normal distribution (Shapiro-Wilks test) or by a non-parametric Mann-Whitney test otherwise.

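### A normality test on the trial data chooses between comparing means and comparing ranks, so the primary effect measure is not fixed in advance

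*Protocol article*

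**What the plan says.** The primary outcome (Outcomes {12}) is "walking speed measured over 10 m at the end of the intervention (6 weeks"). Primary endpoint analysis, under Statistical methods {20a}, describes what will be done with it: "The comparison of the mean walking speed over 10 m measured at the end of the intervention (week 6"). That comparison uses Student's t test "if the variable follows a normal distribution (Shapiro-Wilks test) or by a non-parametric Mann-Whitney test otherwise".

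Sample size {14} works on means only: "The average speed is 0.58+/−0.09 m/s in the control group" and "0.67+/−0.11 m/s in the experimental group". It continues: "The estimated difference between the 2 groups is 0.09 m/s". The Discussion weighs the clinical relevance of that 0.09 m/s against a minimal detectable change of 0.10 m/s in slow walkers, so interpretation is on the m/s scale too.

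The article gives no significance level for the Shapiro-Wilk test. It does not say whether the variable is tested in the two groups together, in each group separately, or on residuals. It names no effect measure to be reported whichever test is chosen. The same rule is repeated for the change in SIPSO score between 6 months and 1 year.

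**The concern.** The t test and the Mann-Whitney test answer different questions. The t test concerns the difference in mean speed, the quantity in the sample size calculation. Mann-Whitney concerns stochastic ordering, that is, the probability that a patient in one group walks faster than a patient in the other. It can be read as a test of a shift in m/s only if the two distributions have the same shape, and the planning SDs (0.09 and 0.11) already differ.

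Under the stated rule, the quantity behind the primary p-value is known only after the outcome data have been tested for normality. At stake is whether the headline result can be set against the 0.09 m/s the trial was designed to detect. This is an explicit rule for the primary endpoint, so an analysis plan that followed it would inherit the problem.

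**Working it through.** **1. Reproduce the planned sample size.** Inputs from Sample size {14}: means 0.58 and 0.67, SDs 0.09 and 0.11, two-sided alpha 0.05, power 90%.

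- Pooled SD = √((0.09² + 0.11²)/2) = √0.0101 = 0.1005.
- n per group = 2 × [0.1005 × (1.960 + 1.282)/0.09]² = 26.2, rounded up to 27, so 54 in all.
- Adding 10%: 54 × 1.10 = 59.4, rounded up to 60.

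The article's 54 and 60 are reproduced by a calculation for a difference in means. Power at 27 per group is 0.908 by the normal approximation and 0.898 by the exact t calculation.

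**2. How often would the rule switch to ranks?** I simulated 27 per group, 6,000 trials per scenario, with Shapiro-Wilk at 0.05. The level is an assumption. Because the article does not say what is tested, both readings were run: groups pooled, and each group separately with a switch if either rejects. The distribution shapes are also assumptions. Means and SDs are those of Sample size {14}.

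| Assumed shape | Switch, pooled | Switch, either group | Power, t test always | Power, Mann-Whitney always | Power, planned rule (pooled / either) |
|---|---|---|---|---|---|
| Normal | 7.8% | 10.1% | 0.902 | 0.881 | 0.898 / 0.898 |
| Gamma | 20.5% | 15.2% | 0.896 | 0.873 | 0.889 / 0.894 |
| Lognormal | 30.9% | 24.8% | 0.907 | 0.889 | 0.900 / 0.906 |
| Strongly skewed (shifted gamma, shape 2) | 87.7% | 90.3% | 0.908 | 0.947 | 0.946 / 0.947 |

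The last row is a stress case, not a forecast.

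**3. Type I error of the rule.** With both means 0.58 and both SDs 0.10:

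| Assumed shape | Pooled | Either group |
|---|---|---|
| Normal | 0.048 | 0.050 |
| Gamma | 0.053 | 0.055 |
| Lognormal | 0.047 | 0.051 |
| Strongly skewed | 0.055 | 0.058 |

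The simulation standard error at 5% is √(0.05 × 0.95/6000) = 0.003.

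**4. Do the two tests disagree?** With the planning means and SDs, they reach the same verdict at the 5% level in about 96% of simulated trials, for both normal and lognormal speeds.

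**5. Does the way the gate is applied matter?** Yes. For gamma data the switch rate is 20.5% pooled and 15.2% by group. Two analysts following the article could therefore run different primary tests on the same data. On the pooled reading, the contrast between groups also enters the normality test: for normal speeds the switch rate is 4.8% with equal means and SDs and 7.8% with the planning values.

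**The case against.** A t test with a rank fallback is a common convention. The rule is written in advance, and Who will be blinded {17a} states that data analysts are blinded, so there is little room for a favourable choice. Error rates and sample size are intact and the two tests usually agree. All of that stands, and it limits the point to interpretability.

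Several stronger readings are tempting but not supported:

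- **That the rule inflates type I error or costs power.** The figures above show no material effect on either.
- **That the rank branch can give no estimate in m/s.** A Hodges-Lehmann shift with confidence interval is in m/s, and nothing in the article forbids reporting group means beside the test. The analysis plan, not shown, may name an estimate. What remains is that the article fixes none, and that a Hodges-Lehmann shift is the mean difference only under a shift model.
- **That normality is tested on the pooled data.** The article does not say; pooled testing is one reading.
- **That a switch is more likely than not.** This needs much wider or more skewed speeds than the article plans for. Its coefficients of variation are 0.09/0.58 = 0.155 and 0.11/0.67 = 0.164.
- **That only the Mann-Whitney branch lacks adjustment for baseline speed or centre.** The planned t test is unadjusted as well, so this does not distinguish the branches.
- **That SIPSO is affected equally.** That secondary endpoint is not sized on a mean difference, so the mismatch with the design does not carry over.

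**Conclusion.** The point holds as a badly fixed rule for the primary endpoint. The comparison is declared as one of means, sized on a mean difference and discussed in m/s, yet a preliminary test on the trial data may replace it with a comparison of ranks. With the planning values and 27 per group, the replacement would happen in about 8-10% of trials if speeds are normal and about 25-31% if they are lognormal. These rates rest on a Shapiro-Wilk level of 0.05 and on assumed shapes, and the ranges span pooled and by-group testing.

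The consequence is that the primary effect measure depends on the data and may not be the 0.09 m/s mean difference the trial was built around. The change is worth making before analysis, because it costs almost nothing and the gate brings little benefit at this sample size.

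**What to change.** In Primary endpoint analysis, delete the Shapiro-Wilk condition. State that the primary result is the difference between groups in mean 10-m walking speed at week 6, in m/s with a 95% CI, whatever the distribution. Estimate it from a linear model with treatment group and the baseline walking speed already collected at the inclusion visit (Participant timeline {13}). Use a robust or bootstrap interval if residuals are clearly non-normal. Report Mann-Whitney as a sensitivity analysis only.

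The sample size stays at 27 per group, 54 evaluable and 60 included. Adjustment for baseline speed can be expected to help precision relative to the unadjusted t test; the documents give no baseline-to-week-6 correlation, so no gain is claimed in figures. The same simplification may be applied to the SIPSO change score, where the case is weaker.

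The cost is a change of wording in the protocol and analysis plan, with no new patients, visits or data.

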#### The following secondary endpoint analyses:

The comparison of the mean difference of the SIPSO score between 6 months and 1 year (T_12M_ – T_6M_) will be performed by means of a Student's t test if the variable follows a normal distribution (Shapiro-Wilks test) or by a non-parametric Mann-Whitney test otherwise.The comparison of the progression of the 4 spatiotemporal parameters selected (duration of the stance and swing phases, step cadence and variability) will be performed using a mixed generalised linear regression.The comparison of the progression of the 2 parameters describing the force of the dorsi-flexor muscles (peak torque in Nm and active amplitude in degrees) will be performed using a generalised linear regression.The comparison of the proportion of patients who used a technical aid will be performed by a Pearson’s chi [2] test or a Fisher’s exact test if at least one theoretical number is <5). The comparison of the number of falls per patient after 6 months will be performed by a binomial negative regression.Correlations between [1] dorsi-flexor muscle strength (2 parameters) and walking speed at 6 weeks, 6 months, and 1 year [2]; dorsi-flexor muscle strength (2 parameters) and SIPSO score at 6 months and 1 year [3]; walking speed and SIPSO score at 6 months and 1 year will be performed using the Pearson or Spearman correlation coefficient test depending on the conditions of application.

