### Objectives {7}

The primary objective is to evaluate the impact of an analytical and repetitive ankle mobilisation programme (combined with conventional rehabilitation including repetitive gait training) on comfortable walking speed over 10 m at the end of the intervention.

The secondary objectives are (1) to evaluate the impact of the programme on social participation at 6 months and 1 year, and to measure its evolution, (2) to evaluate the impact of the programme on the spatiotemporal parameters of walking at the end of the intervention and to measure their evolution at 6 months and 1 year, (3) to evaluate the impact of the programme on the progression of walking speed at 6 months and 1 year, (4) to evaluate the impact of the programme on dorsiflexor muscle strength and to measure its progression over time, at baseline and just after the intervention, along with at 6 months and 1 year of follow-up, (5) to evaluate the impact of the programme on the use of technical aids and on the number of falls between 6 months and 1 year, and (6) to evaluate the relationship between dorsiflexor muscle strength, walking speed and social participation.

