### Methods for additional analyses (e.g. subgroup analyses) {20b}

N/A; no methods for additional analyses.

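### The only between-group test of social participation is the change in SIPSO from 6 months to 1 year, which cancels any benefit gained by 6 months and then kept

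*Protocol article*

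**What the plan says.** - **Objective.** Objectives {7} lists as the first secondary objective "to evaluate the impact of the programme on social participation at 6 months and 1 year, and to measure its evolution". It has two parts: an effect at each of two visits, and how that effect develops.
- **Outcome.** Outcomes {12} defines the matching secondary outcome as "social participation evaluated at 6 months and 1 year". Outcome measurements confirms the timing: social participation "will be evaluated with the Subjective Index of Physical and Social Outcome (SIPSO) at 6 months and at 1 year". The assessments listed under Inclusion (Participant timeline {13}) do not include SIPSO, and no week-6 SIPSO is mentioned.
- **Analysis.** The secondary endpoint analyses under Statistical methods {20a} give one group comparison for SIPSO: "The comparison of the mean difference of the SIPSO score between 6 months and 1 year". It is defined as the 12-month score minus the 6-month score and tested by Student's t or Mann-Whitney.
- **Other use of SIPSO.** The score appears again only in correlations with dorsiflexor strength and with walking speed, for example "walking speed and SIPSO score at 6 months and 1 year will be performed using the Pearson or Spearman correlation coefficient". These do not compare the randomised groups.

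**The concern.** The named contrast answers the evolution part of the objective and leaves the effect at 6 months and at 1 year without a test. A change score normally measures change from a point that treatment has not touched. Here the starting point is the 6-month score, months after the programme has ended, so subtracting it removes whatever the programme had achieved by then.

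Social participation is part of the trial's hypothesis and, in the Discussion, one of the two direct benefits expected. The rationale is that early ankle work brings motor control back sooner. An early gain that lasts is therefore a natural form of success for this programme, and it is the one pattern this test cannot detect. If controls reach the same level later, the test would favour them.

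**Working it through.** **1. The plan's own figure.** The only sample size stated is for walking speed: 0.58 (SD 0.09) against 0.67 (SD 0.11) m/s, two-sided 5%, 90% power.

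- Pooled variance = (0.09² + 0.11²)/2 = 0.0101, so SD = 0.1005.
- n per group = 2 × (1.960 + 1.282)² × 0.0101 / 0.09² = 26.2, rounded up to 27, which gives 54 in total.
- With 10% added, 54 × 1.1 = 59.4, rounded up to 60.

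This reproduces the plan and is not in dispute. It supplies the group size used below. No figure is given for SIPSO.

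**2. What the planned SIPSO test estimates.** Let δ6 and δ12 be the group differences (experimental minus control) in mean SIPSO at 6 months and 1 year.

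E[(T12M − T6M) experimental] − E[(T12M − T6M) control] = δ12 − δ6

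If δ12 = δ6 = δ, this is 0 for every δ. No assumption about the SIPSO mean, SD or within-patient correlation is needed.

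**3. Power when the gain is kept.** The documents give no SIPSO mean, SD, expected effect or correlation, so the standardised effects d (SD 1 at each visit) are assumptions. The test is a two-sample t test, two-sided 5%, with noncentrality d × √(n/2). For example, at d = 0.8 and n = 27 this is 0.8 × √13.5 = 2.94.

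| d at both visits | Comparison at one visit, 27 per group | Same, 30 per group | Planned change test |
|---|---|---|---|
| 0.3 | 19% | 21% | 5% |
| 0.5 | 44% | 48% | 5% |
| 0.8 | 82% | 86% | 5% |

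A simulation of 20,000 trials with 27 per group and d = 0.89 at both visits gave rejection rates for the change test of 4.9%, 5.2% and 4.8% at within-patient correlations of 0.5, 0.7 and 0.9. A comparison at 1 year rejected in about 89% of the same trials.

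**4. When the gain fades.** The SD of the change score is √(2(1 − r)), where r is the assumed correlation between the two SIPSO scores. The noncentrality is (δ12 − δ6)/√(2(1 − r)) × √(n/2), with n = 27.

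| δ6 to δ12 | r | SD of change | Noncentrality | Rejection rate |
|---|---|---|---|---|
| 0.8 to 0.5 | 0.6 | 0.894 | −1.23 | 23% |
| 0.8 to 0.5 | 0.8 | 0.632 | −1.74 | 40% |
| 0.8 to 0.4 | 0.5 | 1.000 | −1.47 | 30% |
| 0.8 to 0.4 | 0.9 | 0.447 | −3.29 | 90% |

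The expected contrast is negative in every row, so the test points towards control although the experimental group has the better mean score at both visits. The same arithmetic applies if the control group catches up between 6 months and 1 year.

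**The case against.** The strongest reply is that the list of secondary analyses is plainly not complete. Walking speed at 6 months and 1 year is also an objective and has no group comparison there, so a fuller protocol or analysis plan may contain a visit-by-visit SIPSO comparison. The statement under Methods for additional analyses {20b}, "N/A; no methods for additional analyses", does not settle this, because that item concerns subgroup and similar analyses. This is fair as far as it goes. But SIPSO, unlike later walking speed, does have an analysis: the article names the contrast, the time points and the test, and the contrast named does not answer the effect half of the objective. That is a choice stated in the document and not a detail left open.

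Two further points stand in part.

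- SIPSO is recorded at both visits, so group scores could be shown beside the test, and a reader could then see a lasting advantage. That softens the consequence. But a comparison at each visit that is introduced after the data are seen would be post hoc, and the named test would still be the formal result.
- The power figures are illustrations. An effect of 0.8 is large for an outcome downstream of walking speed, and at 0.5 a single-visit comparison has only 44% power. The figures also assume that 27 per group are still evaluable at follow-up. The zero expectation under a sustained gain depends on none of this.

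Finally, this is a secondary endpoint: the primary analysis and the sample size are unaffected.

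It could also be argued that a change score is needed because SIPSO has no baseline. It is not. Randomisation makes a comparison of scores at each visit valid without one, and a 6-month score that treatment may already have altered cannot stand in for a baseline.

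**Conclusion.** The concern holds. The planned test covers the evolution of social participation but not the programme's effect at 6 months and at 1 year, which the objective puts first. A gain reached by 6 months and fully kept gives an expected difference of exactly zero, so about 95% of such trials would return a non-significant result however large the gain. This part is algebra and rests only on both scores being post-treatment.

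The size of the loss depends on assumed effects. With 27 per group and a sustained effect, 82% power at either visit falls to 5% for an effect of 0.8, and 44% falls to 5% for an effect of 0.5. A gain that fades from 0.8 to 0.5 would give a significant result in 23% to 40% of trials (assumed correlation 0.6 to 0.8), almost always in the direction of control. The walking-speed conclusion is untouched. The social-participation conclusion cannot be drawn from the analysis as written.

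**What to change.** Replace the SIPSO sentence in the secondary endpoint analyses so that the group difference in SIPSO at 6 months and at 1 year, each with a 95% confidence interval, is the answer to the first secondary objective. Keep the 12-month minus 6-month contrast and label it as the evolution result only.

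The simplest form applies the tests already named to the score at each visit. A better form is one repeated-measures model with group, visit and group-by-visit terms. It gives both visit-specific differences and, through the interaction, the evolution contrast, and it uses patients who have only one of the two scores. Baseline variables already collected, such as walking speed and the Barthel index, can be added for precision. Centre may be considered too, but randomisation is unstratified, and terms for five centres use up information in a trial of 60, so this is optional.

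The cost is a change of wording in the protocol and analysis plan, with no new data, visits or patients. It should be made before the SIPSO data are compared between groups, so that the choice of contrast is not open to question.
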